##### Social control arm

Social activities will include board and team games (e.g. giant Jenga), and group discussions, with the exact activities agreed upon by the group. The purpose of these control activities is to provide a comparative length of time (to the exercise groups) and social context, which does not involve exercise, to estimate any potential social benefits for depression of the two exercise conditions. The Healthy Living session will be the same as other trial arms to avoid introducing variables other than supervised exercise sessions into the study design. Young people in all three arms will be encouraged to engage in physical activity after the intervention ends to maintain their exercise levels.

##### Behaviour change and maintaining engagement

This model of delivery is based on feedback from young people, the team’s experience, and the importance of adherence [50].

Behaviour change techniques (BCT [51];) have been derived using the Behaviour Change Wheel approach, incorporating the COM-B system [52] and the Theoretical Domains Framework (TDF [53]) used as a theoretical base for the ‘Healthy Living’ component of the intervention, e.g. [54]. There are two main objectives of the 15–20 min Healthy Living sessions: (1) to help ensure the young people attend the sessions and engage with the intervention; and (2) to encourage the sustainability of physical activity engagement after the intervention has ended.

These sessions will address key BCTs, delivered through the REPs using Motivational Interviewing and Health Coaching, to promote engagement and enable young people to drive their own goals, learning, and behaviour. The BCTs will use theoretical drivers from the COM-B and TDF to target barriers and facilitators to Capability, Opportunity, and Motivation (see Table 2 for full mapping of theoretical content). Barriers, highlighted by our consultations with young people, include a lack of ‘head space’ or stamina for exercise (Psychological and Physical Capability), lack of social support (Social Opportunity), negative beliefs about exercise (Reflective Motivation), and emotions that lead to avoidance (Automatic Motivation). Potential facilitators were suitable environments (Physical Opportunity) to increase access, manageable sized groups (6–10 young people) and peer support (Social Opportunity), setting goals and increasing positive expectations about exercise (Reflective Motivation). Motivational interviewing (MI) and health coaching will be used to deliver BCTs that will target these barriers and facilitators to enhance intrinsic motivation [57, 58], and address potential depression-related barriers using aspects of behavioural activation, such as activity scheduling and reducing avoidance.

**Table 2 Tab2:** Intervention content mapped from the COM-B to the TDF, intervention functions, policy categories, and behaviour change techniques (BCTs) (based on [51, 53, 55, 56]).

COM-B	Theoretical domain	Intervention function	Policy category	BCTs	Intervention content	Mode of delivery
**CAPABILITY** (Psychological)	Knowledge	Education	Service provision	4.1 Instruction on how to perform the behaviour	The REP will provide instruction on how to perform the activities involved in each session prior to exercising.	Face-to-face group exercise session
				9.1 Credible Source	The REP will be well qualified to deliver exercise sessions, with strong experience and expertise, and will advocate performing exercise during the structured sessions and then promote sustainable physical activity habits after the intervention	Face-to-face group exercise and behaviour change sessions
				2.6 Biofeedback	Participants will be using heart rate monitors to help guide physical effort during the exercise sessions	Face-to-face group exercise session
				5.1 Information about health consequences	Group discussions about health consequences of physical activity	Face-to-face group and behaviour change sessions
	Memory, attention and decision processes	Education	Service provision	1.2 Problem Solving (including relapse prevention)	Group discussions of barriers and solutions to challenges in attending and engaging with the exercise sessions. Towards the end of the intervention, group discussions will prospectively explore potential barriers and solutions to participating in more physical activity after the intervention is finished.	Face-to-face group and behaviour change sessions
	Behavioural regulation	Education	Service provision	2.3 Self-monitoring of behaviour	Encouragement to self-monitor their behaviour with a physical activity diary or a step counter on their phone after the intervention is finished.	Face-to-face group and behaviour change sessions
**CAPABILITY** (Physical)	Skills	Training	Service provision	6.1 Demonstration of the behaviour	The REP will demonstrate the activities involved in each session prior to exercising	Face-to-face group exercise session
				8.7 Graded tasks	The sessions will build in duration (and intensity depending on heart rate feedback), fortnightly, over the 12 week intervention	Face-to-face group exercise session
				8.1 Behavioural practice/rehearsal	The young people will be practising activities at high or low intensity in every session that they attend.	Face-to-face group exercise session
				8.3 Habit formation	Encourage making physical activity habits long term (after the intervention) by trying to perform it in the same context (this could be time/day, activity, or environment)	Face-to-face group and behaviour change sessions
				8.6 Generalisation of the target behaviour	Group discussions on the transition from the exercise classes to wider physical activity after the intervention is finished	Face-to-face group and behaviour change sessions
**MOTIVATION** (Reflective)	Beliefs about capabilities	Persuasion	Service provision	15.3 Focus on past success	Group discussion of examples of past success in terms of previous attendance and engagement with exercise (e.g. school, club, hobbies). Towards the end of the intervention, group discussion will explore of examples of past success in terms of being active in their own time (e.g. hobbies, walking, cycling) to encourage sustainable physical activity habits	Face-to-face group and behaviour change sessions
				15.1 Verbal persuasion about capability	Provide positive talk about the young peoples’ ability to attend and participate in the exercise sessions regularly. Towards the end of the intervention, positive talk will focus on the young peoples’ ability to engage in regular physical activity after the intervention is finished	Face-to-face group and behaviour change sessions
	Beliefs about consequences	Education	Service provision	9.2 Pros and Cons	Group discussions regarding the pros and cons of attending and participating in the exercise sessions. Towards the end of the intervention, group discussions will explore the pros and cons of physical activity after the intervention is finished	Face-to-face group and behaviour change sessions
				5.3 Information about social and environmental consequences	Towards the end of the intervention, group discussions will explore the social consequences of physical activity and the environmental consequences of active travel (e.g. cycling vs car use)	Face-to-face group and behaviour change sessions
				5.6 Information about emotional consequences	Group discussions about the emotional consequences of the structured exercise during the sessions. Towards the end of the intervention, group discussions will explore the emotional consequences of participating in physical activity after the intervention is finished.	Face-to-face group and behaviour change sessions
	Goals	Education	Service provision	1.1 Goal setting (behaviour) 1.4 Action planning	The group will discuss setting detailed plans about incorporating attending the sessions into their weekly routines. Towards the end of the intervention, group discussions will explore setting detailed plans about incorporating physical activity into their weekly routines after the intervention (including signposting local opportunities)	Face-to-face group and behaviour change sessions
				1.5 Review behaviour goal	Encourage reviewing their goals related to the exercise sessions. Towards the end of the intervention, group discussions will encourage reviewing their goals related to physical activity after the intervention is finished	Face-to-face group and behaviour change sessions
**MOTIVATION** (Automatic)	Reinforcement	Incentivisation	Service provision	10.4 Social reward	Young people will be rewarded verbally, providing positive reinforcement, for turning up and participating in the sessions.	Face-to-face group exercise session
				10.9 Self-reward	Encourage rewarding themselves for making progress and/or meeting their goals of engagement with the exercise sessions.	Face-to-face group and behaviour change sessions
				10.7 Self-incentive	Towards the end of the intervention, encourage rewarding themselves for making progress and/or meeting their goals for physical activity after the intervention sessions in the future	Face-to-face group and behaviour change sessions
		Education		5.4 Monitoring of emotional consequences	Encouragement to make mental or physical notes about how they feel during or after the exercise sessions	Face-to-face group and behaviour change sessions
**OPPORTUNITY** (Physical)	Environmental context and resources	Environmental restructuring	Environmental/social planning	12.1 Restructuring the physical environment	The sessions are being added to the young peoples’ environment, for free	Face-to-face group exercise session
				7.1 Prompts/cues	Encouraging young people to leave reminders to prepare for and attend the exercise sessions	Face-to-face group and behaviour change sessions
**OPPORTUNITY** (Social)	Social influences	Environmental restructuring	Environmental/social planning	12.2 Restructuring the social environment	The sessions are being added to the young peoples’ environment, with peers of similar ages, living with depression to provide social support	Face-to-face group exercise session
		Enablement	Service provision	3.1 Social support (unspecified) 3.2 Social support (practical) 3.3 Social support (emotional)	Group discussions of how to ask for and use social support from friends/family/guardians to attend and engage in the exercise sessions if needed. Towards the end of the intervention, group discussions will explore how to build social support for physical activity after the intervention is finished	Face-to-face group and behaviour change sessions
				13.1 Identification of self as role model	Towards the end of the intervention, encourage discussions of how they should think of themselves as role models for exercise for others (friends, family)	Face-to-face group and behaviour change sessions

##### Deliverers and training

The intervention sessions will be delivered primarily by a REP, with a minimum of level 3 qualifications or equivalent, contracted to local community sport and physical activity organisations. A mental health support worker (MHSW) (e.g. an assistant psychologist) will assist the REP in delivering the sessions and will be employed by the local NHS trust. Prior to attending training deliverers will complete the online Good Clinical Practice training from the NIHR [59]. The REPs and MHSWs will then attend 3 days of training (spread over approximately 4 weeks): day 1 will focus on good clinical practice, running the exercise sessions, heart rate monitoring, and research skills related to outcome assessment and data management; the second day will focus on encouraging attendance, adherence, and engagement with the sessions, and longer-term behaviour change; the third day will focus on consolidating the exercise, delivery, behaviour change, and research skill, and mental health training for physical activity promotion.

The training day on behaviour change will cover the ‘healthy living’ behaviour change session content and communication skills using motivational interviewing [60], and how to deliver the BCTs with an emphasis on expressing empathy and being client-focused [61]. This training will highlight the need to engage the young people in the discussions, resist telling them what to do (the righting reflex), allowing focus on what is desired and achievable, to understand their perspective, evoke a sense of empowerment, ensure they feel supported, and have a plan going forward [62]. Core communication skills to support effective group discussions [57, 63] such as RULE (Resist the righting reflex; Understand your client’s motivation; Listen to your client; Empower your client) and OARS (Open-ended questions, Affirmations, Reflective listening, Summaries) will be covered and linked to the delivery of the BCTs. Throughout the delivery period, the REPs and MHSWs will have four further half-day ‘supervision’ workshops to reflect on challenging and successful group discussions and to get expert and peer review of their intervention delivery.

#### Feasibility outcomes

The outcomes for this feasibility trial are:
Referral rate recorded as the number of young people referred for screening via any route by the end of recruitmentRecruitment rate recorded as the number of eligible participants who consent to participate in the study by the end of recruitmentAttrition rate recorded as the number of participants who consent to participate that do not remain in the study until the end of follow-up at 26 weeks post randomisationAttendance rate at the intervention sessions as a proportion of the total number of sessions by 12 weeksHeart rate as measured using a heart rate monitor at each exercise session up to 12 weeksPhysical activity measured using an accelerometer as proportion of time active at baseline, 14 weeks, and 26 weeksAdherence to the intervention protocol as captured by the intervention logs and rated against the adherence checklist by members of the study team at weekly intervention sessions and at 14 and 26 weeksProportion of missing data will be reported as the percentage of recorded outcomes against those expected after account for withdrawal for each outcome separately at 26 weeksAdverse event rate recorded as the frequency, type (injury or clinical progression of depression), and severity of event by treatment arm at 26 weeksEstimate of resource use as measured through observation and study-specific questionnaire at 26 weeksReach and representativeness measured by the proportions of young people who are screened for participation and are randomised in comparison to the characteristics of local populations by the end of recruitment

A traffic-light system, relating to recruitment, retention, adherence, and completion will inform whether we “stop”, “proceed”, or “proceed but with protocol changes” [64]. This system will be judged on criteria including young people’s attendance at sessions > 66% and questionnaire completion > 80% at 14 weeks. Additional process evaluation outcomes are the acceptability of the interventions and questionnaires, barriers and facilitators to engagement of young people, evaluating recruitment methods, and adherence to the intervention protocol by deliverers (fidelity).

#### Participant timeline

Figure 1 shows the flowchart detailing study processes, highlighting the stages leading from participant eligibility assessment to final data analysis.

**Fig. 1 Fig1:**
[figure not shown]
Study flowchart

#### Sample size

Eighty-one eligible young people from three English counties (27/county; Hertfordshire, Bedford, and Norfolk) were selected. This sample size was selected to enable 20 participants per arm to attend the intervention sessions (assuming 33% dropout) and allows for each of the 3 interventions to be completed at each of the 3 study sites, giving 9 groups in total. Each group needs to have 9 participants to ensure that at any given session at least 6 participants are present (allowing for 33% no show/drop out). As this is a feasibility study it is not powered to detect a difference in clinical outcomes between the two intervention arms and the social control arm. Therefore, no power calculation has been performed. A sample size of 81 participants will allow us to gain experience in running each intervention at each site. It will also allow us to estimate the outcome completion rate to within ± 6% assuming a completion rate of 80% using an 80% confidence interval.

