### Assignment of interventions

Eligible participants who have consented to the study will be allocated to groups of approximately 9 participants, and each group will be randomised into one of the three trial arms (Table 3). This clustering is designed to limit waiting time for young people to start the intervention to minimise the dropout rate. Each group will either be a single-sex group or will include at least two girls and two boys. The former was deemed essential by patient and public involvement (PPI) representatives from diverse cultural heritage.

**Table 3 Tab3:** Study schedule

	Study period						
	Screening	Randomisation	Post-randomisation				Post-randomisation follow-up
TIMEPOINT	Pre-T0	Pre-T0	T0	T0-T1	T1 +14 weeks	T2 +26 weeks	

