#### Statistical methods

Data analysis for the feasibility study will be largely descriptive. The referral, recruitment (> 10% of potential young people recruited), and retention (> 66% attendance at intervention sessions) will be evaluated, reporting the proportions (and confidence intervals) of young people reaching each stage of the study, by referral source and study arm. Reach and representativeness will be described in relation to the proportions of young people who are screened for participation and are randomised, and in comparison, to the characteristics of local populations. Adherence will be assessed through the proportions of sessions attended and the average heart rate achieved compared to the target for the intervention. Behaviour change, in terms of increased physical activity beyond the intervention sessions, will be measured by accelerometer and self-report data at 14 and 26 weeks. Feasibility of collecting outcome and resource use data will be evaluated by estimating the proportions of missing data in each of the outcomes assessed. The outcome measures will be summarised, by study arm, using descriptive statistics based on the intention-to-treat principle. No formal comparison of the groups will be made. To monitor safety, the number of adverse events will be reported by study arm. 

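### At the stated 33% dropout, 27 participants per arm leave about 18 attending, not the 20 per arm given as a basis for the sample size

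*Protocol article*

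**What the plan says.** All the figures are in the Sample size section of the protocol article. The total is "Eighty-one eligible young people from three English counties", 27 from each. The section gives the attendance basis: "This sample size was selected to enable 20 participants per arm to attend the intervention sessions (assuming 33% dropout"). It adds that the number "allows for each of the 3 interventions to be completed at each of the 3 study sites, giving 9 groups in total". For the size of each group it says: "Each group needs to have 9 participants to ensure that at any given session at least 6 participants are present", followed by the qualifier "allowing for 33% no show/drop out".

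The section on assignment of interventions confirms the structure. Participants are "allocated to groups of approximately 9 participants, and each group will be randomised into one of the three trial arms".

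The trial is not sized on a clinical effect: "Therefore, no power calculation has been performed". The Sample size section closes with a separate precision statement for the outcome completion rate: ±6% at 80% completion, using an 80% confidence interval.

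**The concern.** Two sentences in the same section use the same 33% and imply different numbers per arm. One says that 20 will attend. The other plans for six present in each group, and with three groups per arm that makes 18. A reader who applies 33% to 27 also gets 18.

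Twenty per arm is one of the reasons given for choosing 81, so the document claims a property that the design does not have on its own assumption. There is also a forward risk. The Objectives say that this trial will inform the sample size of the main trial. If the 27 came from the wrong inflation formula and that formula is used again, the main trial would be short as well.

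The group sentence has a smaller wording problem. It presents as assured, at every session, a number that is an expected value when 33% is read as an average rate.

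**Working it through.** **Inputs (Sample size section).** Total N = 81; 3 arms; 3 sites; 9 groups; 9 per group; target 20 attending per arm; dropout d = 0.33; planned minimum of 6 present per group.

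**1. Reproducing the planned size.**
- Layout: 9 groups × 9 = 81. Each arm has 3 groups, so 3 × 9 = 27 per arm. This agrees with the document.
- From the target of 20 with the correct inflation, n / (1 − d): 20 / 0.67 = 29.85, so 30 per arm and 90 in total. This does not give 27 or 81.
- From the target of 20 with n × (1 + d): 20 × 1.33 = 26.6, so 27 per arm and 81 in total. This matches exactly, but it is the wrong formula. The match suggests how 27 arose; the document does not show the calculation.

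**2. What 27 per arm delivers.**
- 27 × (1 − 0.33) = 27 × 0.67 = 18.09. With d = 1/3 the result is 18.0.
- From the group sentence: 3 groups × 6 present = 18.
- Shortfall against the stated figure: 20 − 18 = 2 per arm (10%), or 60 − 54 = 6 in total.

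**3. What 20 per arm would require.**
- Keeping 27 per arm: d ≤ 1 − 20/27 = 0.259, about 26%.
- Keeping d = 0.33: 30 per arm, 90 in total, or 10 per group in nine groups.

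**4. If the same formula were carried forward.** Inflating by (1 + d) and then losing a fraction d leaves n(1 + d)(1 − d) = n(1 − d²). At d = 0.33 this is n × (1 − 0.1089) = 0.891n, about 11% below target before rounding up. Here, 20 × 0.891 = 17.8, and rounding 26.6 up to 27 lifts it to 18.1.

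**5. Group size.** 9 × 0.67 = 6.03. The six in the document is therefore right as an expected number.

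**6. Precision statement.** The 80% interval half-width at 80% completion with n = 81 is 1.2816 × √(0.8 × 0.2 / 81) = 0.057, consistent with the stated 6%. It uses 81 and does not depend on 20 per arm.

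**The case against.** The best defence is that little depends on the number. This is a feasibility trial with no power calculation, the gap is two participants per arm, and no analysis, decision rule or precision statement in the article uses 20 per arm. Running each intervention at each site and the ±6% precision are separate grounds for 81, and both survive. All of this stands and fixes the severity as minor. It does not make 20 correct.

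It can also be said that the group sentence states a planning allowance: nine less a third is six. That arithmetic is right, so only the strength of the wording is open to comment.

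A reader might infer three stronger points that the document does not support:

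- **That about a third of sessions would fall below six.** If nine people attend independently with probability 0.67, the chance of at least six is 0.66. But the 33% explicitly includes dropout, which is permanent and so correlated across sessions. If three of nine left and the other six always came, every session would have exactly six. The document gives no basis for the independence model.
- **That average attendance would be about four.** This applies 33% twice (9 × 0.67 × 0.67 = 4.0). The group sentence gives one combined allowance for no-shows and dropout.
- **That a trial performing as planned would be judged infeasible.** Neither 20 per arm nor six per session is among the progression criteria shown. Attendance is judged against a threshold of more than "66% attendance at intervention sessions", and the planning rate of 67% would pass. The list of traffic-light criteria is not presented as exhaustive, but none that is shown uses these figures.

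**Conclusion.** The point holds as an arithmetic error in a stated basis for the sample size. At 33% dropout, 27 per arm yields about 18 attending and not 20, which is 54 rather than 60 in total. The section's own group figures confirm the 18. This rests only on the document's inputs and on equal arms of three groups of nine; taking 33% as one third changes nothing material. That the cause was multiplying by (1 + d) is an inference from an exact match.

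The wording on six per session is secondary: six is the expected number and is not assured.

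Severity is minor. The nine-by-nine layout, the precision statement and the progression criteria shown are unaffected, and the error does not show that 81 is too few for the trial's feasibility aims.

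**What to change.** Keep 81 and correct the sentence in one of two ways:

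- *27 per arm; with 33% dropout, about 18 per arm are expected to attend*; or
- keep 20 per arm and state the dropout that it requires, about 26%. This choice also needs reconciling with the 33% used for group size.

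In the group sentence, replace the assurance of at least six at any session with *so that about 6 are expected per session*. Do not write binomial session frequencies into the protocol, because they would present an unsupported independence assumption as a trial expectation.

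When sizing the main trial, inflate for dropout by dividing by (1 − d).

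The cost is wording only. No extra participants are needed and no change to groups, sites or analysis; the stated attendance figure becomes slightly less favourable.

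### The ±6% precision for the completion rate assumes 81 independent participants, although the trial randomises, treats and mostly assesses them in nine groups

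*Protocol article*

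**What the plan says.** The Sample size section of the protocol article sets the number mainly on logistical grounds. The total of 81 "allows for each of the 3 interventions to be completed at each of the 3 study sites, giving 9 groups in total", and "Each group needs to have 9 participants to ensure that at any given session at least 6 participants are present". No power calculation is made, which is reasonable for a feasibility trial. One precision statement is then added: the sample will allow the team to "estimate the outcome completion rate to within ± 6% assuming a completion rate of 80% using an 80% confidence interval". No ICC or design effect is given, and independence is not mentioned.

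Other sections describe the structure of the data:

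- Trial design calls this a cluster randomised trial.
- Under Assignment of interventions, participants are "allocated to groups of approximately 9 participants, and each group will be randomised into one of the three trial arms".
- Under Baseline and follow-up, outcome data are planned to be collected with each trial group together. Individual online completion is available to those who prefer it.
- Feasibility outcomes names questionnaire completion above 80% at 14 weeks among the criteria for progression. It separately defines missing data against the outcomes expected once withdrawals are taken into account.

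**The concern.** The stated error margin belongs to a simple random sample of individuals, but this design samples groups. Members of a group share an exercise professional, a support worker, a venue and a timetable. They also share the follow-up session at which most questionnaires are expected to be completed. If a session goes badly or is poorly attended, several questionnaires are likely to be lost together. Completion is therefore an outcome for which some within-group correlation should be expected.

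Positive correlation means that 81 participants carry the information of fewer than 81 independent ones. With no power calculation, the ±6% is the only statistical precision offered for the sample size. It is also evaluated at the same 80% that serves as a progression criterion. A reader who takes it at face value will think the completion rate is known more firmly than it will be.

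**Working it through.** **Inputs from the protocol article.** Sample size: n = 81, nine groups, m = 9 per group, assumed completion p = 0.80, 80% two-sided confidence level (z = 1.2816). The ICC is not in the document. It is an assumption here, shown over 0.01 to 0.20.

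**Step 1: reproduce the stated figure.**
Half-width = z × sqrt(p(1 − p)/n) = 1.2816 × sqrt(0.16/81) = 1.2816 × 0.0444 = 0.0570, or 5.7 points, which rounds to 6. A Wilson interval gives the same 5.7. The arithmetic is right for independent participants.

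**Step 2: allow for the groups.**
Design effect DE = 1 + (m − 1) × ICC = 1 + 8 × ICC. Half-width = 5.70 × sqrt(DE). Effective sample size = 81/DE.

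| Assumed ICC | DE | Effective n | 80% half-width (points) |
|---|---|---|---|
| 0 | 1.00 | 81 | 5.7 |
| 0.01 | 1.08 | 75 | 5.9 |
| 0.02 | 1.16 | 70 | 6.1 |
| 0.05 | 1.40 | 58 | 6.7 |
| 0.10 | 1.80 | 45 | 7.6 |
| 0.20 | 2.60 | 31 | 9.2 |

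**Step 3: find where the stated figure stops holding.**
Solve 5.70 × sqrt(1 + 8 × ICC) = h for the ICC.
- h = 6.0: ICC = ((6.0/5.70)² − 1)/8, about 0.014.
- h = 6.5: ICC = ((6.5/5.70)² − 1)/8, about 0.038.

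So the half-width passes 6.0 at an ICC of about 0.014 and no longer rounds to 6 above about 0.04.

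**Step 4: the small number of groups.**
If the interval is built from nine group-level results with a t multiplier on 9 − 1 = 8 degrees of freedom, the half-widths at ICC 0.05, 0.10 and 0.20 become 7.3, 8.3 and 10.0 points.

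**Step 5: what an unadjusted interval would deliver.**
The actual coverage of a nominal 80% interval that ignores the groups is 2Φ(1.2816/sqrt(DE)) − 1. This is about 72%, 66% and 57% at ICC 0.05, 0.10 and 0.20. It applies only if such an interval is used.

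**The case against.** **The effect may be small.** The ICC is unknown, and at 0.01 or 0.02 the half-width is 5.9 or 6.1, which still rounds to 6. The option of individual online completion may weaken the correlation. This stands: the documents do not prove that the true half-width exceeds 6 points. They do give a reason to expect some correlation and none to assume exactly zero.

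**The figure is ancillary.** The sample size follows from nine groups and the wish to "enable 20 participants per arm to attend the intervention sessions (assuming 33% dropout"), and the analysis is descriptive. This also stands, and it keeps the point modest. It does not make an independence-based margin right for a clustered design.

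**The interval method may be in the statistical analysis plan.** That plan was not available, and Statistical methods does not say that intervals will ignore the groups. An unadjusted interval is therefore a risk, not a stated plan. The precision figure itself is stated in the protocol and can be judged as it is.

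Three stronger readings are tempting but not supported:

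- **A reader might infer that the 33% dropout cuts n to 54.** That percentage is given for attendance at intervention sessions, not for questionnaire return. If completion is counted over everyone recruited, a dropout is a non-completer and n stays 81. Losing a third of questionnaires would also cap completion at about 67%, at odds with the assumed 80%. Only if withdrawals on that scale left the denominator would n be about 54, with a half-width of 7.0 points before clustering.
- **A reader might set the per-arm precision against the stated ±6%.** With 27 per arm the half-width is 1.2816 × sqrt(0.16/27) = 9.9 points before clustering, but Sample size claims precision only for the overall rate. The commitment in Statistical methods to "reporting the proportions (and confidence intervals) of young people reaching each stage of the study, by referral source and study arm" concerns referral, recruitment and retention. Questionnaire completeness is dealt with in a separate sentence.
- **A reader might infer that the interval drives the progression decision.** Feasibility outcomes lists thresholds and does not say that a confidence limit enters the judgement.

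**Conclusion.** The point holds in its clustering form. The ±6% is computed correctly for 81 independent participants, but it omits the design effect of a trial with nine groups of about nine. Under any positive ICC the precision is worse than the 5.7 points calculated. The loss is trivial at an ICC of 0.01. It is about 1 point at 0.05 (6.7 against 5.7), about 2 points at 0.10 (7.6) and 3.5 points at 0.20 (9.2).

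These sizes rest on equal groups of nine, 80% completion, all 81 in the denominator and an assumed ICC. The protocol does not say which denominator the ±6% uses, and this should be settled when the figure is restated. The consequence is an overstated precision, not a flaw in the sample size or the design.

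**What to change.** 1. In Sample size, replace the single figure with a range and state its basis. For example: with nine groups of nine and 80% completion, the 80% half-width is 5.7 points if responses are independent, and about 7 to 8 points for an assumed ICC of 0.05 to 0.10. Label the ICC as an assumption.
2. In the same place, say whether participants who withdraw stay in the denominator of the completion rate, and whether the 14-week progression criterion uses that denominator.
3. Calculate the confidence intervals for completion and attendance so that they allow for the nine groups. Suitable methods are group-level proportions with a t multiplier, or a Wilson interval adjusted by a design effect. Report the observed spread between groups, which would also help in planning the main trial. If the statistical analysis plan already does this, only items 1 and 2 remain.

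The cost is a sentence or two of wording and a few lines of analysis code. The stated precision becomes slightly less favourable. Recruitment, number of groups and conduct are unaffected.
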